## Objectives {7}

The main objectives are to investigate the efficacy of intensive exposure-based treatment (iPE) for PTSD in a randomized controlled trial (*N* = 140) comparing iPE with weekly delivered prolonged exposure. The trial will encompass an assessment of health-economic factors from two distinct viewpoints: one from the standpoint of the treatment provider (comprising direct expenses such as healthcare personnel costs) and the other from a more extensive societal standpoint (encompassing indirect expenses such as sick leave). Additionally, we will measure treatment-related transformational processes and factors that can influence treatment results.

The two types of treatment formats will be compared 1 month after treatment completion in each respective treatment arm (primary endpoint) and at the 6-month and 12-month follow-ups regarding clinician-rated PTSD symptom severity by assessors masked to treatment allocation. In addition, comparisons in relation to self-rated symptoms of PTSD and complex PTSD, depression and quality of life, recovery rate, response and remission rates, number of dropouts, cost-effectiveness, adverse events, treatment mediators and moderators, credibility, satisfaction with treatment, and perceived alliance with the therapist will be made. Due to its shorter format, we expect the intensive treatment format to provide a faster response than first-line treatment.

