The research questions to be answered within the project are as follows:Is iPE more efficacious than weekly delivered sessions of prolonged exposure regarding reduction of blinded assessor rated PTSD symptom severity 1-month posttreatment in each respective treatment arm?Is iPE more cost-effective than weekly delivered sessions of prolonged exposure at 1 month, 6 months, and 12 months posttreatment?Does iPE lead to less dropout than weekly delivered sessions of prolonged exposure up to 1 month posttreatment?Does iPE lead to more adverse events than weekly delivered sessions of prolonged exposure up to 12 months posttreatment?Does iPE lead to a faster recovery rate than weekly delivered sessions of prolonged exposure up to 12 months posttreatment?Is iPE more efficacious than weekly delivered sessions of prolonged exposure regarding the reduction of self-rated depression and increased quality of life at 1 month, 6 months, and 12 months posttreatment?What is the mechanism of change of prolonged exposure? Does the mechanism of change in iPE and weekly delivered sessions differ?What are the moderators of the treatment effect?Are the therapeutic gains of iPE maintained at long-term follow-up (6 and 12 months after treatment)?

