## Trial design {8}

The trial uses a single-blind (assessors masked to treatment allocation), randomized (1:1), controlled, parallel-group, superiority design comparing intensive prolonged exposure and first-line treatment for adults with PTSD residing in Sweden. We aim to recruit 140 participants who will be assessed before treatment start, during treatment, 1 month after treatment completion in each respective treatment arm (primary endpoint), and at follow-ups 6 and 12 months after treatment completion. The flow chart of the trial is shown in Fig. 1.

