### Eligibility criteria {10}

To ensure the study’s external validity, we will adopt broad inclusive eligibility criteria. Participants presenting with comorbidities such as neuropsychiatric disorders, depression, and substance abuse will be evaluated for inclusion based on meeting all other specific inclusion/exclusion criteria. The primary diagnosis for inclusion will be PTSD.

Please see Table 1 for a comprehensive outline of the inclusion and exclusion criteria.

**Table 1 Tab1:** Inclusion and exclusion criteria

Inclusion criteria	≥ 18 years of age
	Primary diagnosis of PTSD according to DSM-5
	Signed informed consent
	Able to attend either iPE or 15 weekly sessions of PE
	Being fluent in Swedish
Exclusion criteria	Initiation or adjustment of any psychotropic medication within the last 4 weeks prior to inclusion
	Serious mental health symptoms, such as mania, psychosis, alcohol, or substance use disorders or current suicide risk warranting immediate clinical attention
	Ongoing evidence-based trauma-focused psychological treatment
	Ongoing trauma-related threat (e.g., living with a violent spouse)

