Secondary self-rated outcome measures are the Post-traumatic Stress Disorder Checklist for DSM-5 (PCL-5; [12]) and the International Trauma Questionnaire (ITQ; [13, 14]). These instruments are utilized to capture self-rated symptoms of PTSD and complex PTSD. Treatment response on the PCL-5 will be defined as a reduction of 10 points or more from the baseline score. Remission will be determined by a score below 30 on the PCL-5, as identified in the Swedish version of the scale by Bondjers [15], which is indicative of probable PTSD. To be classified as having achieved recovery, participants must maintain their remission status through the subsequent follow-up assessment.

Additionally, the level of depressive symptoms will be assessed using the Patient Health Questionnaire (PHQ-9; [16, 17]), and quality of life will be assessed using the EQ-5D [18].

The Assessing Quality of Life 6 Dimensions (AQoL-6D; [19]) will be administered to calculate quality-adjusted life-years for cost-utility analysis. The Treatment Inventory of Costs in Psychiatric Patients will be used to collect information on the use of medical resources, medication, social care, absenteeism, and presenteeism (TIC-P; [20]).

The Negative Effects Questionnaire (NEQ; [21]) will be used to capture potential adverse events immediately after treatment completion and the upcoming assessment points. An open-ended question asking for the occurrence of any adverse events will also be administered at each treatment session.

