### Participant timeline {13}

Applicants register on an encrypted study platform that uses a two-step authentication where information about the study and the informed consent form can be found. Prospectively eligible applicants will undergo a thorough assessment of eligibility using the MINI, CAPS-5, and a structured suicide risk evaluation assessment. Eligible participants will be invited to participate in the study if the inclusion criteria are met, as stated in Table 1.

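### PCL-5 remission and recovery carry no baseline condition, so a participant who enters below 30 and stays there counts as a success without improving, which dilutes the between-arm difference.

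*Protocol article*

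**What the plan says.** In the protocol article, Outcomes {12} gives three binary definitions on the PCL-5.

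- Response: "Treatment response on the PCL-5 will be defined as a reduction of 10 points or more from the baseline score".
- Remission: "Remission will be determined by a score below 30 on the PCL-5". The section links this cut-off to probable PTSD in the Swedish version of the scale.
- Recovery: "To be classified as having achieved recovery, participants must maintain their remission status through the subsequent follow-up assessment".

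Only response refers to the baseline score, and it is not joined to remission or recovery.

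On entry, Table 1 under Eligibility criteria {10} asks for "Primary diagnosis of PTSD according to DSM-5" and sets no minimum PCL-5. Participant timeline {13} describes a "thorough assessment of eligibility using the MINI, CAPS-5, and a structured suicide risk evaluation assessment". The PCL-5 is not among the eligibility instruments, and Table 3 first schedules it at baseline.

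Objectives {7} lists "recovery rate, response and remission rates, number of dropouts" among the planned comparisons between arms. It also poses the research question "Does iPE lead to a faster recovery rate than weekly delivered sessions of prolonged exposure up to 12 months posttreatment".

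**The concern.** Entry is decided by diagnostic interview and clinician rating, whereas remission here is decided by a self-report score. Nothing in the text makes a diagnosed participant score 30 or more on that self-report at baseline. One who enters at 27 and remains at 27 meets the remission rule at every assessment and the recovery rule at the next one, yet never meets the response rule. One who worsens from 20 to 29 also counts as remitted.

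Such participants contribute successes that treatment did not produce. The reported remission and recovery rates then overstate improvement in both arms. The contrast between arms, which is what the planned comparisons are about, is diluted.

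**Working it through.** The protocol states no expected rate, power or sample size for PCL-5 remission or recovery, so there is no figure of its own to reproduce. The check is a reading of the definitions, followed by an illustration.

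**Inputs from the document.** Remission is a score below 30. Recovery is remission maintained. There is no PCL-5 entry minimum. Planned size: "We aim to recruit 140 participants", allocated 1:1, so 70 per arm.

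**Assumptions, not in the document.** f is the share of each arm that enters below 30 and stays there. p is the true remission rate among those entering at 30 or more.

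**Formula.** Observed rate in an arm = f + (1 − f)p. With the same f in both arms, the first term cancels and the observed difference = (1 − f) × (p_iPE − p_weekly).

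**Illustration 1: assumed true rates 60% and 45%, difference 15 points.**

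| f | iPE | Weekly PE | Difference |
|---|---|---|---|
| 5% | 0.05 + 0.95 × 0.60 = 62.0% | 0.05 + 0.95 × 0.45 = 47.75% | 14.25 points |
| 10% | 0.10 + 0.90 × 0.60 = 64.0% | 0.10 + 0.90 × 0.45 = 50.5% | 13.5 points |
| 15% | 0.15 + 0.85 × 0.60 = 66.0% | 0.15 + 0.85 × 0.45 = 53.25% | 12.75 points |

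The loss is 0.75 to 2.25 points.

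**Illustration 2: power, assumed true rates 60% and 40%, 70 per arm, two-sided 0.05.** Without low entrants, power is 66.1%.

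| f | Difference, rule as written | Power, rule as written | Power, restricted to baseline 30 or more |
|---|---|---|---|
| 2% | 19.6 points | 64.3% | 65.2% |
| 5% | 19.0 points | 61.7% | 63.8% |
| 10% | 18.0 points | 57.3% | 61.4% |
| 20% | 16.0 points | 48.9% | 56.4% |

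Restriction returns the difference to 20 points at every f. It recovers only about half of the lost power, because the denominator shrinks (at f = 10%, from 70 to 63 per arm).

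**Sensitivity to staying low.** If 10% enter below 30 but only 90% of them stay there, equally in both arms, the rates are 63% and 45%. The difference is still 18 points. The shrinkage depends on how many enter low, not on all of them staying low.

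**Would a 10-point fall, added to the score below 30, serve instead?** Take f = 10% and Illustration 1, and suppose the low entrants do not fall by 10 points. They become failures but remain in the denominator: 0.90 × 60% = 54% against 0.90 × 45% = 40.5%, a difference of 13.5 points. That equals the difference under the rule as written. The condition would also stop counting a participant who moves from 35 to 28 as remitted.

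**The case against.** The strongest case against runs as follows. The share f has no source, and the document points to a small one: every participant has diagnosed PTSD, and the cut-off is tied to probable PTSD. The proportion below 30 among all randomised participants is a valid marginal contrast. It looks shrunken only against a restricted population. The protocol deliberately separates end state (remission) from change (response), so a reader who sets the two side by side can tell who improved. The analytic plan on OSF, cited under Statistical methods {20a}, is not shown and might already restrict the denominator.

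Most of this stands as a limit on size. It does not remove the gap. Remission and recovery are fixed here as outcomes in their own right, and separate response rates do not show which remitted participants were already below 30 at entry. If the OSF plan already restricts the denominator, the protocol's definition should be brought into line with it.

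Three stronger readings are tempting, and the document does not support them.

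- A reader might infer bias towards one arm. Randomisation balances low entrants in expectation, so for the rates this is dilution.
- A reader might infer that low entrants have their recovery event at time zero. No time-to-event analysis with baseline as a possible event time is described.
- A reader might infer that daily PCL-5 ratings in the intensive week would make low entrants seem to recover sooner in iPE. That depends on how events are dated, and also on which scale measures recovery speed, and the document settles neither.

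**Conclusion.** The point holds as a minor flaw in a secondary outcome definition. As written, PCL-5 remission and recovery can be met without improvement, and the risk difference is multiplied by (1 − f). An assumed 15-point difference becomes 14.3 to 12.8 points for an assumed f of 5% to 15%. Both f and the remission rates are assumptions, and the true f may lie below that range. The result also assumes that f is equal in the two arms, which randomisation secures only in expectation. The CAPS-5 primary outcome and the sample size built on it are unaffected, and the protocol makes no power claim for PCL-5 remission or recovery.

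**What to change.** State in Outcomes {12} that PCL-5 remission and recovery, including any speed-of-recovery analysis based on the PCL-5, are analysed among randomised participants with a baseline PCL-5 of 30 or more. Report by arm the number entering below 30. Keep the all-randomised proportion as a supplementary figure.

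Define baseline as the PCL-5 score recorded before allocation. Sequence generation {16a} places randomisation after the baseline assessment, but the columns of Table 3 put allocation first. Participants are not blinded, so a restriction on a score given after allocation would lose the protection of randomisation.

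The change takes a line or two and no new data. The price is a slightly smaller denominator and slightly lower headline rates (in Illustration 1 at f = 10%, 60% and 45% in place of 64% and 50.5%). It should be made before any analysis by arm.

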#### Treatment variables

Participants will also be asked to state their treatment format preference pre- and posttreatment on a 7-point Likert-type scale. Data will also be collected on the number of attended sessions for each participant (including any additional time needed, for example, phone calls between sessions) and protocol deviations. Ratings of the patient’s subjective level of distress for each exposure treatment session will also be collected. Treatment credibility and working alliance will be evaluated between the treatment arms with the Credibility/Expectancy Questionnaire (CEQ; [22]) and Working Alliance Inventory–Short Form Revised (WAI-SR; [23]).

A treatment completer is defined as a participant who completed all treatment sessions or recovered early. Early recovery is defined as a participant who demonstrates a positive response after at least 6 treatment sessions involving imaginal exposure, with a minimum of a 10-point reduction on the PCL-5. Both the participant and therapist must mutually agree to terminate the treatment.

Participants who drop out or recover early from the treatment will be encouraged to continue to participate in the study and all the outcome assessment points.

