**WALK OUTSIDE** 12:00 – 12:30	**GROUP SESSION 2** **IN-VIVO EXPOSURE** 12:00–13:45	**GROUP SESSION 3** **IN-VIVO EXPOSURE** 12:00–13:45	**GROUP SESSION 4** **IN-VIVO EXPOSURE** 12:00–13:45	**GROUP SESSION 5** **IN-VIVO EXPOSURE** 12:00–13:45
Break 12:30 – 13:00				
**IMAGINAL EXPOSURE SESSION 1** 13:00 – 14:00				
	Break 13:45 – 14:00	Break 13:45 – 14:00	Break 13:45 – 14:00	Break 13:45 – 14:00
Break 14:00 – 14:15	**IMAGINAL EXPOSURE SESSION 3** 14:00 – 15:00	**IMAGINAL EXPOSURE SESSION 5** 14:00 – 15:00	**IMAGINAL EXPOSURE SESSION 7** 14:00 – 15:00	**IMAGINAL EXPOSURE SESSION 9** 14:00 – 15:00
**OWN WORK** 14:15 – 15:15				
	Break 15:00 – 15:15	Break 15:00 – 15:15	Break 15:00 – 15:15	Break 15:00 – 15:15
	**OWN WORK** 15:15 – 16:15	**OWN WORK** 15:15 – 16:15	**OWN WORK** 15:15 – 16:15	**OWN WORK** 15:15 – 16:15

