#### Weekly prolonged exposure

Patients will receive 15 weekly 90-min sessions of individual prolonged exposure for PTSD according to the standard treatment delivery protocol. In session 1, a comprehensive overview of treatment rationale will be provided, along with the selection of the index trauma, which will be the focus of imaginal exposure and breathing retraining. Session 2 will include psychoeducation on trauma and PTSD, along with a rationale for in vivo exposure and the construction of an in vivo hierarchy. In session 3, imaginal exposure including processing for the trauma will commence following an overall rationale of this core treatment component. Starting from session 4 and continuing through session 14, participants will engage in imaginal exposure during the sessions and continue in vivo exposures outside of the therapy sessions. Assigned homework during the treatment weeks will include reading treatment material, practice breathing retraining, listen to recordings of imaginal exposure, and conducting in vivo exercises. Session 15 will include a summary of the treatment and lessons learned, as well as relapse prevention and planning of continued self-practice.

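### The completer rule labels an agreed early stop at the PCL-5 response threshold as recovery, against the protocol's own recovery definition, and takes such stops out of the dropout count

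*Protocol article*

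**What the plan says.** Under Treatment variables, "A treatment completer is defined as a participant who completed all treatment sessions or recovered early". The next sentence gives the conditions, of which the first concerns sessions: "Early recovery is defined as a participant who demonstrates a positive response after at least 6 treatment sessions involving imaginal exposure". The size of the response needed is then fixed on the self-rated scale: "with a minimum of a 10-point reduction on the PCL-5". A further condition follows: "Both the participant and therapist must mutually agree to terminate the treatment". The same section then names those who drop out and those who recover early as two different groups, so an early recoverer is not a dropout. The article gives no other definition of dropout.

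A few paragraphs earlier in Outcomes {12}, a PCL-5 reduction of at least 10 points from baseline is defined as treatment response. For the higher categories, "Remission will be determined by a score below 30 on the PCL-5", and "To be classified as having achieved recovery, participants must maintain their remission status through the subsequent follow-up assessment".

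Dropout up to 1 month posttreatment is a research question in Objectives {7}. Sample size {14} gives it a separate power simulation. Who will be blinded {17a} states that therapists cannot be blinded.

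**The concern.** One threshold carries two names with different consequences. In the outcome definitions a 10-point fall is the lowest grade of improvement. In the completer rule the same fall, with the session and agreement conditions, is called recovery and turns an early stop into completion.

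This reaches a comparison that the protocol treats as important. Lower dropout is part of the rationale for the intensive format, and the Discussion names it in the case for implementing iPE. If participants who are still above the protocol's remission cut-off can stop early and be counted as completers, the dropout rate no longer shows how many people left before the end of the course. Two participants with the same attendance and the same PCL-5 change can also fall on different sides of the count, depending on whether the therapist agreed to the stop. The CAPS-5 is protected by masked assessors, but this classification has no such protection.

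**Working it through.** **1. The two definitions applied to one participant.** Take a PCL-5 of 55 at baseline and 45 after six imaginal sessions, with an agreed stop.

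- Reduction: 55 − 45 = 10, which meets the response definition.
- Distance from the remission cut-off: 45 is 15 points above 30, so not remitted and hence not recovered under Outcomes {12}.
- Under Treatment variables: recovered early, a completer, not a dropout.

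**2. The plan's own power figure.** Inputs from Sample size {14}: 22% versus 5%, 140 participants, linear regression conditional on four strata. Two-sided alpha of 0.05 and equally likely strata are assumed. Simulation gives 0.871 (5000 runs) and 0.876 (4000 runs), against 0.878 stated. An exact enumeration of the pooled z-test with 70 per arm gives 0.87. The stated figure reproduces and is not in question.

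**3. Where the six-session condition falls in each arm.**

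- Weekly PE: "In session 3, imaginal exposure including processing for the trauma will commence" and it continues through session 14, which makes 12 imaginal sessions. The sixth is session 8, so 7 of 15 sessions remain (47%).
- iPE: nine imaginal sessions in the week plus three boosters that include imaginal exposure, also 12. By Table 2 the sixth is on Thursday morning. Group sessions 4 and 5, imaginal sessions 7 to 9 and three boosters remain: 8 of 5 + 9 + 3 = 17 (47%).
- In calendar time, about 4.4 of 5 weeks remain in iPE (88%) and 7 of 15 weeks in weekly PE (47%).

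**4. What relabelling could do to the comparison.** The documents do not say what share of stops would qualify. As an illustration, let a share s of the stops made after the sixth imaginal session be relabelled, and treat 22% and 5% as rates before relabelling. The observed rate is then true rate × (1 − share of course remaining × s). For weekly PE at s = 0.25 this is 22% × (1 − 0.47 × 0.25) = 19.4%. Power is by exact enumeration, 70 per arm.

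| Assumption | s = 0.25 | s = 0.50 | s = 0.75 |
|---|---|---|---|
| Stops spread over sessions (47% and 47%) | 19.4 v 4.4%: 0.82 | 16.8 v 3.8%: 0.76 | 14.2 v 3.2%: 0.68 |
| Stops spread over calendar time (47% and 88%) | 19.4 v 3.9%: 0.86 | 16.8 v 2.8%: 0.85 | 14.2 v 1.7%: 0.85 |
| Weekly stops only relabelled | 19.4 v 5%: 0.77 | 16.8 v 5%: 0.64 | 14.2 v 5%: 0.47 |

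Applying a relabelled share to all stops, by simulation of the regression model, widens the range. Half of weekly stops only gives 11% versus 5% and power of about 0.25. Half of iPE stops only gives 22% versus 2.5% and about 0.97.

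Now suppose the true stop rate is 20% in both arms. The calendar spread produces an apparent iPE advantage of 17.7 − 15.6 = 2.1 points (s = 0.25) to 13.0 − 6.8 = 6.2 points (s = 0.75). The spread over all sessions produces at most 0.06 points.

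**The case against.** The strongest reply is that the rule is narrower than it first looks, and defensible. A participant who simply walks away after a 10-point fall is not an early recoverer, because six imaginal sessions and mutual agreement are also required. Treating an agreed stop after a good response as something other than dropout is a reasonable concept. Recovery in the outcome section depends on a later follow-up and could not be known on the day treatment ends, so the two uses of the word may serve different purposes. Attended sessions are recorded, dropout is a secondary outcome, and the analysis plan is a separate file that is not shown here.

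Most of this stands, and it limits the point. It does not remove the conflict: the article itself fixes a completer rule in a term that it defines otherwise a few paragraphs earlier, and the rule does not require the PCL-5 to be below 30 at the stop.

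A reader might go further and infer that the rule favours iPE, because the exemption opens on day 4 of a five-week course there and only at session 8 of 15 in weekly PE. The documents do not support this. By imaginal sessions the condition is 6 of 12 in both arms, and by all scheduled sessions about 47% remain in each. The arms differ only in calendar time, and four of the five iPE weeks contain nothing but three boosters. Nothing in the protocol says that stops would spread evenly over those weeks. A reader might also infer a specific loss of power. The fall to 0.77–0.47 appears only if weekly stops alone are relabelled. With the calendar shares applied to both arms, power stays at 0.86–0.85. Nor does the article say whether 22% and 5% already use the completer rule; if they do, there is no loss.

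**Conclusion.** The inconsistency is confirmed from the text and needs no assumption: an early stop that meets only the response threshold is called recovery and counted as completion, whether or not the participant is below the remission cut-off. It follows that some early stops by participants still above that cut-off leave the dropout count for research question 3, and that an unblinded therapist's agreement is part of what decides this.

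The effect on the arm comparison cannot be sized. The illustrative power values run from about 0.25 to 0.97, according to which stops are assumed to be relabelled, and the direction is equally open. That spread is not evidence of bias. It shows only that the answer could depend on a share that nobody has specified. The change should be made, but the primary CAPS-5 comparison is not affected by this point.

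**What to change.** - Reconcile Treatment variables with the definitions in Outcomes {12}. One way is to label the 10-point category early response, so that recovery has a single meaning. The rule for ending treatment is for the sponsor to reconcile; no change to it is proposed here.
- For research question 3, report three groups by arm: attended all sessions; stopped early with the last PCL-5 below 30; stopped early otherwise.
- Prespecify a dropout analysis that counts every stop before the last scheduled session, regardless of therapist agreement, alongside the analysis under the existing completer definition.

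No new data are needed. Attended sessions are already recorded, and Table 3 schedules the PCL-5 during treatment in both arms, daily in the intensive week. The cost is a wording change, one extra analysis and somewhat higher reported dropout rates. Replacing the rule outright with a PCL-5 cut-off that ignores agreement would be a debatable trade: a participant who stops attending without agreement at 29 would not count as dropout, while an agreed stop at 31 would. Reporting both definitions avoids that choice. The wording should be settled before analysis begins, which Trial status places at October 2025.
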